## Ethical considerations

The CABMILK study protocol, participant information sheet, and informed consent documents have been reviewed and approved by the National Health Sciences Research Committee (NHSRC) of Malawi (approval reference 24/10/4527), with institutional ethical oversight from the Malawi-Liverpool-Wellcome Research Programme Clinical Research Support Unit (CRSU). The study will be conducted in accordance with the Declaration of Helsinki (2013) and ICH Good Clinical Practice (E6 R2, and R3 as applicable). Any protocol amendments will be submitted to the NHSRC before implementation, and serious adverse events will be reported within the regulatory timelines.

### The informed consent process

During consenting, the literacy level of the mother will be assessed by first asking her whether she would be willing to read and explain a brief statement in the consent form. To minimise undue bias of socioeconomic status within the study population, mothers who are unable to read or write will still be considered for participation in the study as long as the mother understands the participant information sheet (PIS) and there is an impartial witness during the informed consent process to ensure that the mother is provided with correct and complete information. The mother will be asked if they are comfortable with this arrangement. The impartial witness will be someone who is not directly involved with the study e.g. a companion of the mother or another health worker from the government health facility who is literate. Informed consent will be obtained using the following process:
•The potential participant (mother) will be invited into a private space to discuss the consent form with a study nurse in their local language.•The study nurse or study physician or principal site investigator will review the form with the potential participant and assess understanding of the study by asking the participant to repeat the main message of each part of the consent form. Every effort will be made to explain the process and procedures of the study in a language that the participant could understand.•In cases where a potential participant displays a clear lack of understanding of the aim of the study, procedures, time commitment, risks and benefits, assessed through question-and-answer sessions, and after several attempts to clarify them, the study personnel will be allowed to make a judgement not to continue with the consent process. To avoid causing embarrassment to the mother, the study personnel will be required to decide with the mother by highlighting that on initial assessment, it would appear that the study may not be suitable for her or her child.•The study personnel will then provide time for the mother to ask any questions that she may have and will make a record of these questions and the responses that are given. The mother will be given the PIS to take home to read or discuss the information with any other person (if they wish), including members of their family, friends or a healthcare worker that they see routinely. They will be requested to allow the study team to contact them the following day, either through a mobile phone or home visit, for the participant to ask any further questions and to communicate their decision.•If the mother agrees to participate in the study, she will be asked to sign the consent form in the presence of the study personnel, and an impartial witness if the participant is illiterate. As consenting is a continued process, study nurses will continue to confirm, verbally, the mother’s willingness to continue participating in the study at each study visit.

### Withholding information

No information will be withheld from the study participants. Any relevant new findings will be shared with the National Health Sciences Research Committee (NHSRC) and study participants, with re-consenting as appropriate.

### Risk of study participation: venous sampling, breastmilk sampling, finger/heel pricks and mitigation of potential injury

Participants will undergo repeated needle and finger/heel pricks in this study, than they normally would, but in line with standard hospital procedures in relation to blood sample collection. The risks of these procedures include pain, transient bleeding, and soft tissue infection. A small bruise or mild pain at the site from where the blood is taken may develop. To mitigate this risk, only well-trained study staff will be hired for the project. Additionally, only new disposable needles and lancets will be used for the blood collection procedures, which will be safely discarded immediately after use. Furthermore, breastmilk manual expression, as part of sampling, may be associated with some minimal risk of discomfort in mothers and the need for privacy. To mitigate this, all mothers will be supported by trained study team members to manually express breastmilk comfortably. In addition, all sampling occasions will be conducted in a private room/space to ensure comfort and maintain privacy.

### Recommended infant blood sample volume

Infant blood will be collected using calibrated micro-collection EDTA tubes, and each infant will contribute five blood samples (
Figure 2). The total infant blood volume will not exceed 5 mL for all blood sampling time points. This volume is safe for an infant as per NIHR guidelines that state that that blood volume limits for sampling, per individual (including study-related blood loss and any losses in the manoeuvre), should not exceed 3% of the total blood volume in a period of four weeks, and should not exceed 1% at any single time. For a 5 kg infant, this equates to 4 mL per sample/at a single sampling time point or 12 mL over 4 weeks.
^
20
^ A total infant blood volume of 5 mL for all blood sampling time points in the CABMILK study is therefore safe. In all study procedures, loss of blood or excess blood sample collection will be minimized, during sampling, by using calibrated capillary and venous collection tubes.

### Benefits of participation in the study

The direct benefit of participation in the CABMILK study is that infants would be closely monitored, and this would be particularly valuable in this sub-population, which is at higher risk of general childhood illnesses. The indirect benefit is that the study is envisaged to provide evidence on the safety of cabotegravir breast milk exposure during childhood. Although the burden of research to inform the safety of breastmilk exposure to cabotegravir is being borne by the participants in this study, the evidence will likely inform policy and practice and thereby be applied to a wider population.

### Privacy and confidentiality

During this study, medical history and physical examination will be performed at baseline and regular intervals. All the materials collected are for research purposes only, and data will be kept in strict confidence. No information will be given to anyone without permission from the subject. The consent form includes the informed consent statement which guarantees confidentiality. Confidentiality will be ensured using identification codes assigned to the study participants. All data, whether generated in the laboratory or at the bedside will be identified using an identification code unique to the subject. The data managers at MLW will combine the baseline, pharmacokinetic data and follow-up data into a final data set which will be password protected. Handling and processing of data will be according to data protection legislation in Malawi.

### Duration of sample and data storage

All samples (breastmilk and blood) will be collected in duplicates; one backup at the Malawi-Liverpool Wellcome Programme (MLW) /UNC Project laboratory and the other shipped for cabotegravir assay. The maximum period of sample (backup sample) and data storage at MLW will be five years following the completion and publication of the study findings.

### Dissemination and data sharing plan

Community engagement in CABMILK was initiated at study set-up and continue throughout implementation. Sensitisation meetings were held with hospital staff, and later with community leaders, and residents in the catchment areas of the participating health centres. Ongoing engagement will take place through listening sessions with enrolled mothers and caregivers in Chichewa at the under-five and postnatal clinics, and through community-engagement activities broadly organised by the institution’s Community Engagement Department aimed at increasing visibility in Lilongwe, where its research activities are not yet well established. From these activities, we aim to enhance enrolment and retention in the CABMILK study. These CABMILK-specific activities are distinct from, but co-delivered with, the broader community-engagement architecture of the parent PathToScale and LINK studies. These activities ensure that the study remains transparent, culturally grounded, and responsive to community needs.

Community engagement forms the backbone of the CABMILK study. Initial sensitisation meetings will be held with hospital staff, community leaders, and residents to introduce the study and address early questions. Ongoing engagement will continue through outreach at government-supported under-five and postnatal clinics, small-group discussions in local languages, and a dedicated community radio program developed with health educators. These activities ensure that the study remains transparent, culturally grounded, and responsive to community needs.

Scientific dissemination will focus on contributing to the global evidence base for HIV prevention in lactating women. The findings will be submitted to reputable peer-reviewed journals and shared at major international conferences, including the IAS. Additional methodological outputs, such as breast milk pharmacokinetic analyses and safety signal detection models, will be published as preprints and made accessible through open science platforms.

To support policy and programmatic decision-making, tailored briefs and technical summaries will be provided to the Malawi Ministry of Health, the NHSRC, and other national stakeholders. The results will be presented in multisectoral learning sessions to inform national CAB-LA rollout and strengthen maternal–child health pharmacovigilance. A key output will be early algorithms for detecting potential safety concerns in infants exposed to cabotegravir through breast milk, with the aim of integrating these into routine monitoring systems.

Public dissemination will prioritise accessibility and clarity. Lay summaries, infographics, and materials in English and Chichewa will be shared through health facility posters and digital platforms such as social media and WhatsApp. Engagement with community advisory boards and mother support groups will ensure that the findings are understood and can inform community dialogue.

Data sharing will follow open science principles, while protecting participants’ confidentiality. Aggregated datasets, breastmilk pharmacokinetic summaries, and analysis codes will be shared on Wellcome Open Research and an MLW-managed repository. De-identified individual-level data will be available upon reasonable request under a governed access model. Protocols, analysis plans, and metadata will be openly accessible to support reproducibility and wider scientific use.

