### Missed visits

All dosing visits for injectable and oral PrEP are aligned with those of the parent PathToScale and LINK implementation studies. As the CABMILK study is leveraging the platform of the implementation of PathToScale and LINK studies, missed dosing or follow-up visits are inevitable. Nevertheless, any such missed dosing or follow-up visits, including sample collection visits, will be conducted as soon as it is possible to do so. This will be documented appropriately in the participant’s file.

Retention and evaluable pairs: The primary pharmacokinetic analysis will be conducted on mother–infant pairs who contribute matched maternal plasma, breastmilk, and at least one infant dried blood spot sample within the month-7 window. Losses before the month-7 sampling visit, missed CAB-LA doses, and out-of-window sampling will be documented and reported as implementation outcomes. Baseline characteristics of mothers who do and do not reach the evaluable PK sampling visit will be compared descriptively. Retention is supported through appointment reminders, alignment of CABMILK visits with routine postnatal and under-five clinic contacts, travel reimbursement, and, where acceptable to the mother, a home visit to complete a missed sampling occasion. Recruitment will continue until the target of 25 evaluable pairs in the CAB-LA group has been met bearing in mind study timelines.

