To profile the extent of CAB transfer in breast milk and determine its pharmacokinetics in infants whose mothers receive long-acting injectable cabotegravir for HIV preexposure prophylaxis (PrEP).	We will use non-linear mixed effects models to determine the compartmental pharmacokinetics of CAB from maternal plasma to breast milk to infant plasma. We will first calculate the milk: plasma ratio to determine the average milk CAB concentration compared with the average maternal plasma concentration. Second, we will utilise individual predicted infant CAB concentrations to calculate infant overall exposure (AUC0-∞) and estimate CAB infant half-life as well as elimination rate constant. Third, we will estimate the CAB dose ingested by each infant, through breast milk, relative to the maternal dose; the relative infant dose (RID). ^ 25 ^ This RID will allow us to determine the extent of CAB breast milk exposure that would result in attained concentrations in the infant’s blood that are above or below the protein-adjusted IC90 of 0.166 μg/mL. ^ 26 ^	CAB transfer to the infant through breast milk, and profile the attained infant concentrations.
To determine the association of breast milk CAB exposure and infant safety outcomes (growth pattern, neuro-cognitive development, and incidence of adverse events).	Firstly, mean anthropometric indices (weight-for-height, height-for-age, head circumference-for-age) will be compared across three groups using independent t-tests. Secondly, adverse events (overall morbidity) by the end of follow-up will be compared across the three groups using Chi-squared tests. Age-standardised CREDI summary scores (z-scores) analysed as continuous outcomes, reported as adjusted mean differences with 95% confidence intervalsUsing linear regression, we will assess whether breast milk CAB concentrations predict growth patterns and morbidity, adjusting for infant age, sex socio-economic status, birth weight and gestation age at birth. Random effects models will account for intra- and interindividual variability in repeated measurements. Exploring this analysis may inform algorithms for monitoring CAB safety signals in infants. These algorithms could be validated in larger studies and incorporated into routine practice for early detection of CAB-related risks in infants.	Impact of CAB breast milk exposure on infant growth and neurocognitive development in comparison to the standard daily oral PrEP.

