## Limitations

This study has several limitations. Enrolment from birth to five months spans a period of rapid ontogeny of Uridine Diphosphate Glucuronosyltransferase 1A1 (UGT1A1)-mediated glucuronidation and developmental change. Although population pharmacokinetic modelling incorporating maturation functions and age-standardised growth and developmental outcomes will be used, the small number of infants within age strata limits precision in characterising exposure–age relationships; findings at younger ages should therefore be interpreted with caution. Secondly, the study is not powered to detect between-group differences in infant safety, growth, or developmental outcomes, and these analyses are consequently descriptive and hypothesis-generating, with formal inference deferred to larger studies. Thirdly, infant feeding patterns and maternal nutritional status may influence infant exposure; feeding will be captured longitudinally and incorporated as a time-varying covariate, while maternal weight will be evaluated in relation to cabotegravir clearance and milk-to-plasma ratios. However, the study does not directly measure milk composition or detailed maternal dietary intake, limiting the ability to fully assess indirect dietary effects. Finally, as exposure groups are self-selected, comparative analyses are observational and exploratory, and although adjusted and sensitivity analyses will be undertaken where feasible, residual confounding cannot be excluded.

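### Infant safety-detection algorithms are promised as a key output for routine monitoring, which goes further than Table 2 and a regression in about 25 infants can support; linear regression also does not suit adverse events

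*Protocol article*

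**What the plan says.** The protocol article mentions the algorithms in two places, with different strength.

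- **Dissemination and data sharing plan:** "A key output will be early algorithms for detecting potential safety concerns in infants exposed to cabotegravir through breast milk". The intended use follows in the same sentence: "with the aim of integrating these into routine monitoring systems". No validation step is attached here. The same section says that safety signal detection models will be published.
- **Data analysis, Table 2, second objective:** a linear regression asks whether breast milk cabotegravir concentration predicts growth patterns and morbidity, "adjusting for infant age, sex socio-economic status, birth weight and gestation age at birth". Random effects are to handle repeated measurements. The table then says: "Exploring this analysis may inform algorithms for monitoring CAB safety signals in infants". It continues: "These algorithms could be validated in larger studies and incorporated into routine practice for early detection of CAB-related risks in infants".

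The same row of Table 2 equates adverse events with overall morbidity.

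The rest of the article sets a modest frame. The broad objective calls the safety description preliminary and non-inferential. The sample-size section calls comparative analyses exploratory and says the study cannot detect subtle differences or rare events. Limitations says that the study is not powered for between-group differences and that "these analyses are consequently descriptive and hypothesis-generating".

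Table 1 lists breast milk sampling for Group A (CAB-LA) only. Missed visits gives the number: "Recruitment will continue until the target of 25 evaluable pairs in the CAB-LA group has been met bearing in mind study timelines".

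**The concern.** The two passages describe different products. Table 2 treats an algorithm as something that might follow from an exploratory analysis and would need validation elsewhere. The dissemination plan makes it a deliverable aimed at routine monitoring and omits the validation step. A reader who takes only the dissemination plan, such as a ministry or a funder, would expect a usable rule from this study.

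The design gives little ground for one. The only analysis named as a source has six predictors and about 25 infants, and its sample size was set for the pharmacokinetic step. A fitted model of that size can look informative in its own data and still fail in new infants.

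A second, smaller problem concerns the outcome. Adverse events are a count or a yes/no variable. A straight line with constant normal error suits neither, and it ignores differences in follow-up time.

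**Working it through.** The article gives no sample size, R-squared or performance target for this regression, so there is no stated figure to reproduce. The check asks what a model of this size can do.

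**Inputs**

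- n = 25: target number of evaluable CAB-LA pairs (Missed visits); milk sampled in Group A only (Table 1).
- p = 6: milk concentration plus infant age, sex, socio-economic status, birth weight and gestational age (Table 2), each taking one degree of freedom.
- One outcome value per infant, ordinary least squares. Normally distributed predictors are assumed for the new-infant formula.

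**1. In-sample R-squared if nothing is associated**

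R-squared follows Beta(p/2, (n-1-p)/2) = Beta(3, 9), with mean p/(n-1) = 6/24 = 25.0%. The median is 23.6% and the 95th percentile 47%. A simulation of 20,000 data sets gave a mean of 25.2%.

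**2. Prediction error in new infants**

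Expected squared error, relative to the residual variance, is (1 + 1/n) x (n-2)/(n-p-2) = 1.04 x 23/17 = 1.407.

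For a true R-squared of rho2, the expected new-infant R-squared is 1 - (1 - rho2) x 1.407:

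| True R-squared | New-infant R-squared |
|---|---|
| 0 (complete null) | -0.41 |
| 0.10 | -0.27 |
| 0.20 | -0.13 |
| 0.30 | 0.02 |
| 0.40 | 0.16 |
| 0.50 | 0.30 |

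Break-even with the population mean is at 1 - 1/1.407 = 0.29. Against the mean of the 25 infants themselves it is 1 - 17/23 = 0.26.

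**3. Sensitivity**

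- Fewer infants: null in-sample R-squared is 6/21 = 28.6% at n = 22 and 6/19 = 31.6% at n = 20. At n = 20 the error factor is 1.05 x 18/12 = 1.575, and break-even rises to 1 - 1/1.575 = 0.37.
- Socio-economic status with 2 or 3 degrees of freedom at n = 25: 7/24 = 29.2% or 8/24 = 33.3%.
- Six visits per infant pooled as rows (assumed within-infant correlation 0.5 to 0.85): simulated null R-squared falls to about 12% to 18%. The number of infants does not change.
- All 100 infants, with concentration set to zero in the unexposed: 6/99 = 6.1%. The text does not plan this, and it would be largely a group comparison.

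**4. The milk-concentration slope**

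With five other covariates, power for a partial correlation r is approximately Phi(atanh(r) x sqrt(25-5-3) - 1.96). At r = 0.60 this is Phi(0.693 x 4.123 - 1.96) = Phi(0.90) = 0.82. Only a strong association would be detected reliably.

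**5. Linear regression for adverse events**

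The article gives no event rate. Under an assumed mean of about 1.5 events per infant with overdispersion, simulated coverage of the 95% interval for the slope was 92.7%, and 99% of 95% prediction intervals reached below zero. The slope suffers little. Individual prediction, which a detection rule needs, suffers more.

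**The case against.** The strongest reply is that the article does not claim what a critical reader might infer. Three stronger readings are tempting, and the text supports none of them.

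- *The fitted equation is the monitoring rule.* No section says so. Table 2 says the analysis may inform algorithms, and the dissemination plan names no source model.
- *An untested tool goes to the Ministry of Health.* What goes there is briefs and technical summaries. Routine integration is stated as an aim, the algorithms are called early, and Table 2 mentions validation: "These algorithms could be validated in larger studies and incorporated into routine practice".
- *Any such model would be mostly noise.* The 25% and -0.41 belong to the complete null with one value per infant. Birth weight, gestational age and age may well relate to growth. At a true R-squared of 0.5 the model would predict usefully.

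It is also fair that R-squared is not the study's target. Five of the six terms are adjustment covariates, and the quantity of interest is the milk-concentration slope with its interval. With 25 - 7 = 18 residual degrees of freedom, that interval keeps its nominal coverage under the usual model. The short covariate list elsewhere in Data analysis belongs to the longitudinal growth and CREDI models, so Table 2's longer list does not plainly contradict it. How many covariates to use is a judgement for the investigators.

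All of this stands. It does not remove the mismatch between a firm key output without a validation condition and a tentative possibility with one. It also does not make a linear model suitable for adverse events.

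**Conclusion.** The point holds as an inconsistency between sections and one badly chosen model. The dissemination plan promises more than Table 2 says and more than the objectives, sample-size and Limitations sections allow. The regression named as the possible source could beat the mean in new infants only if the true R-squared exceeded about 0.3. That figure assumes 25 infants, six single-degree-of-freedom predictors, one outcome value per infant and normally distributed predictors. Fewer infants or more degrees of freedom make it worse. The 25% in-sample and roughly -0.4 new-infant values apply only to the complete null and should be cited as such.

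Linear regression for adverse events is wrong for the type of outcome, but its effect on the slope interval looks modest under the assumed event rate. The number of adjustment covariates is not part of the error.

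**What to change.** 1. **Dissemination and data sharing plan:** remove algorithms as a key output. Alternatively, restate them as hypotheses for a monitoring rule that must be developed and validated in a separate, larger data set before any routine use.
2. **Table 2, second objective:** use the same wording, so that validation is a condition and not a possibility. Report the milk-concentration slope with a 95% confidence interval for each outcome and label it exploratory.
3. **Adverse events in Table 2:** replace linear regression with a Poisson or negative binomial model with a person-time offset, or logistic regression if the outcome is yes/no. Linear models can stay for the growth indices.

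No data collection changes, so this can be done while enrolment continues. The cost is wording in two places, a slightly different model for one outcome, and one promised output fewer.
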